### Intervention

The intervention is based on the Transtheoretical Model (TTM) [32, 33] and will be made by physicians and nurses in the routine care of PHC practices according to the conceptual framework of the “5A’s”: Assess, Advise, Agree, Assist, and Arrange-follow up [34]. It will consist of a first visit of screening in which PHC professional will assess person level of behaviour and stage of change (“Assess”). Behaviours will be assessed by one question to know tobacco use during the last month, two validate questions about the daily consumption of fruits and vegetables [35] and the Brief Physical Activity Assessment Tool [36, 37]. Stages of change will be assessed on the basis of core constructs of the TTM for each of the target behaviours (see Table 1) [32]. Subsequently, the PHC professional will advise the person (“Advise”), will agree with him/her on a realistic set of goals (“Agree”), will assist to anticipate barriers and will develop a specific action plan (“Assist”), and will arrange follow-up support (“Arrange”).

**Table 1 Tab1:** Core constructs of the Transtheoretical Model (Prochaska et al. 2008) [32]

Stages of Change	Description
Precontemplation	No intention to take action within the next 6 months
Contemplation	Intends to take action within the next 6 months
Preparation	Intends to take action within the next 30 days and has taken some behavioural steps in this direction
Action	Changed overt behaviour for less than 6 months
Maintenance	Changed overt behaviour for more than 6 months
Termination	No temptation to relapse and 100% confidence

Intervention is based on the results of previous phases (preclinical, phase I and phase II) [23–25, 38–42]. It will have a maximum duration of 12 months and it will be carried out to three different levels (individual, group and community) according to stages of change and unhealthy behaviour (see Table 2). It will focus on all three target behaviours and PHC professional together with the participant will develop priority actions on one or more of these behaviours.

**Table 2 Tab2:** Description of intervention

	Unhealthy behaviours								
	Tobacco use			Insufficient physical activity			Non-adherence to Mediterranean dietary pattern		
Level of intervention	Individual	Group	Community	Individual	Group	Community	Individual	Group	Community
Stages of change									
Precontemplation	Very brief intervention + SMS			Very brief intervention + SMS			Very brief intervention + SMS		

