#### i) Effectiveness outcomes

The effectiveness of the complex multiple risk behaviour intervention in comparison with the usual care at maximum 12 months post-intervention will be measured by:
*Primary outcome measures*
Positive change in baseline eating behaviour: adherence to the Mediterranean dietary pattern in low adherence people. For the evaluation, the 14-item Questionnaire of Mediterranean diet adherence (PREDIMED study) will be used [49]. The positive change has been defined as obtaining eight or fewer points at the study entry and nine or more at the end of the study in this questionnaire.Positive change in baseline physical activity behaviour: sufficient physical activity level in insufficiently active people. For the evaluation, the International Physical Activity Questionnaire will be used [50]. The positive change has been defined as having a low physical activity level at the study entry and a moderate or high physical activity levelat the end of the study.Positive change in baseline smoking behaviour: self-reported continuous abstinence [51]. For the evaluation, the interview will be used and optionally the cooximetry. The positive change has been defined as smoking at the study entry and not smoking at the end of the study. We will measure the punctual and continuous abstinence at these two times.

*Secondary outcome measures*

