Beginning or making a behaviour change. The proportion of people who are in the stages of action, maintenance or termination according to the TTM at the study entry and at 12 months.Change from baseline on sedentary behaviour. It will be measured by the sitting items from the International Physical Activity Questionnaire.Change from baseline on diet quality. Diet Quality Index-International will be used to determine diet quality [52].Change from baseline on health-related quality of life. It will be measured by the EuroQol-5D questionnaire [53].Reduction of the cardiovascular risk. The proportion of people with low/moderate and high/very high baseline cardiovascular risk who have reduced it. Cardiovascular risk will be calculated using REGICOR [54, 55] and SCORE [56] function charts.Change from baseline on body mass index. Body mass index is defined as the body weight divided by the square of the body height and is expressed in units of kg/m^2^.Change from baseline on waist circumference. The waist circumference will be measured at a level midway between the lowest rib and the iliac crest. It will be expressed in units of cm.Change from baseline on blood pressure. It will be measured in the routine clinical practice by validated electronic monitors and it will be expressed in units of mmHg.Change from baseline on lipid profile. The lipid profile will include: low-density lipoprotein, high-density lipoprotein, triglycerides and total cholesterol. They will be expressed in units of mg/dl.Change from baseline on arterial stiffness. Arterial stiffness will be assessed by the “Cardio-Ankle Vascular Index”. It will be measured by the Vascular Screening System VaSera VS-1500 N or VaSera VS-2000.Change from baseline on theankle-brachial index. It will be measured by the Vascular Screening System VaSera VS-1500 N or VaSera VS-2000.Change from baseline on the “REgicor and Artper Score fOr aNkle brachial index (REASON)” [57].Change from baseline on the perceived functional social support. The questionnaire Duke-UNC-11 will be used to determine the perceived functional social support [58–60].Reduction of the incidence of major depression will be evaluated by CIDI interview [61].Reduction of the risk of depression in participant non-depressed at baseline. Risk of depression will be calculated using the algorithm PredictD [62].Reduction of depression symptoms. The Patient Health Questionnaire-9 will be used to determine the prevalence and the severity of depression symptoms [63].Reduction of anxiety symptoms. The General Anxiety Disorder-7 questionnaire will be used to determine the prevalence and the severity of anxiety symptoms [64].Change from baseline on unhealthy behaviours of professionals of the PHC intervention centres.

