### Data collection and management

Data will be collected at PHC centre, professional and participant levels. Data collection methods and procedures are summarised in Table 4.

**Table 4 Tab4:** Schedule of Data Collection Methods and Procedures

			Pre-implementation/Pre-study consent/screening	During implementation			Post-implementation
Activity/Assessment	Data collection	Responsible		Study baseline	Intervention visits	Follow-up 12-months	
PHC centre level							
Characteristics of assigned people	Form report	Research team each autonomous community	x				
Organisational structure	Form report	Research team each autonomous community	x				
Survey of Organizational Attributes for Primary Care	Self-administered questionnaire	Research team each autonomous community	x				x
Professional level							
Age, sex, academic education and experience in PHC	Self-administered questionnaire	Research team each autonomous community	x				
Daily consumption of fruits and vegetables/Level of physical activity/Smoking behaviour	Self-administered questionnaire	Research team each autonomous community	x				x
Appropriateness and acceptability	Self-administered questionnaire	Research team each autonomous community	x				x
Determinants of implementation (CFIR constructs)	Focus group	Research team each autonomous community					x
Participant level							
Informed consent	Paper document	PHC professionals	x				
Age and sex	CRF	PHC professionals	x				
Screening unhealthy behaviours	CRF	PHC professionals	x				
Inclusion/Exclusion criteria	CRF	PHC professionals	x				
Adherence to the Mediterranean dietary pattern	CRF (14-item Questionnaire of Mediterranean diet adherence	External unit of local trained personnel		x		x	
Quality of diet	CRF (Diet Quality Index-International)	External unit of local trained personnel		x		x	
Physical activity behaviour	CRF (International Physical Questionnaire)	External unit of local trained personnel		x		x	
Smoking behaviour	CRF (interview and optional cooximetry)	External unit of local trained personnel		x		x	
Stage of change	CRF	PHC professionals (intervention group)		x		x	
		External unit of local trained personnel (control group)		x		x	
Health-related quality of life	CRF (EuroQol-5D questionnaire)	External unit of local trained personnel		x		x	

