At PHC centre level, we will collect information related to: assigned population (total number; average age; distribution by age group and sex; percentage of immigrants; deprivation index; prevalence of tobacco use; level of physical activity and number of people allocated to home care), organisational structure (population coverage; average attendance; number of physicians, nurses and social workers; accreditation as training health centre; participation in undergraduate and postgraduate training; average visits per day; population per health professional; average time per visit and participation research experience). We will also measure the PHC centres’ internal resources for change by the “Survey of Organizational Attributes for Primary Care” [70].

At the professional level, personal data will be collected (age, sex, academic education and experience in PHC). PHC professionals will have to complete a self-administered questionnaire. This questionnaire collects information about professionals’ behaviours with reference to tobacco use, daily consumption of fruit and vegetables and level of physical activity. In addition only in health professionals of intervention centres, it includes nine items to measure the perception of appropriateness and acceptability of the intervention; these items are based in questionnaires which measure similar constructs [71].

Participant-level data are described in Table 4. Recruitment, first screening for entrance to the study and intervention visits will be done by health professionals. Data collection at participant level will be supported by an external unit of local trained personnel who will carry out two visits (baseline and at the 12 months) in each PHC centre because they are not considered as usual care tasks. Data will be collected by means of an online CRF specially designed for the study. This CRF will be pilot tested in pre-implementation stage (see Table 3). The management of the study is based on a central coordination unit, a regional coordination unit and a PHC coordination unit using different periodic communication methods (meetings, teleconferences, e-mails, etc.).

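### Stage of change, a secondary between-arm outcome, is recorded by treating staff in the intervention arm and by the external unit in the control arm, so an arm difference cannot be separated from an assessor difference

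*Protocol article*

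**What the plan says.** Four places in the protocol article bear on this.

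- **Outcome.** Under Effectiveness outcomes, the secondary list opens with "Beginning or making a behaviour change. The proportion of people who are in the stages of action, maintenance or termination according to the TTM", taken at entry and at 12 months. The section introduces its outcomes as measuring "The effectiveness of the complex multiple risk behaviour intervention in comparison with the usual care".
- **Who records it.** Table 4 (Data collection and management) splits the stage-of-change row by arm: "PHC professionals (intervention group)" and "External unit of local trained personnel (control group)". Both lines are marked at baseline and at the 12-month follow-up.
- **Who those professionals are.** The Intervention section says that the intervention "will be made by physicians and nurses in the routine care of PHC practices", and that at the first visit the "PHC professional will assess person level of behaviour and stage of change". Staging is thus also the step that decides which intervention a participant receives.
- **Who else is present.** The same data-collection section describes "an external unit of local trained personnel who will carry out two visits (baseline and at the 12 months) in each PHC centre". Table 4 gives this unit the diet, physical activity, smoking, quality-of-life, cardiovascular, depression and anxiety measures, with no split by arm.

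The section on assignment states that there is no blinding. The Analysis section plans hierarchical models for each outcome and does not mention the assessor.

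**The concern.** A randomised comparison of an outcome is fair only if the outcome is measured in the same way in both arms. Here the person asking, the setting and that person's relation to the participant all change with the arm. In the intervention arm, participants report their progress to staff of the team that counselled them, and those staff know the allocation. In the control arm, they report to someone with no part in their care.

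Stage of change is open to this kind of influence. Table 1 of the article defines the stages by intention, reported change and confidence. The outcome's cut lies between preparation, which already includes some behavioural steps, and action, which requires changed behaviour. Whether a participant's steps count as change can depend on who asks and who records. At stake is whether a difference in this one secondary outcome can be read as an effect of the intervention.

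**Working it through.** The plan states no figure on this point, so the check is first a comparison of sections and then an illustration of size.

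**1. Is assessor fully tied to arm?** Table 4 gives one assessor type per arm at both time points, with no overlap and no duplicate rating. In any regression, an assessor indicator would equal the arm indicator, so the two effects cannot be estimated separately. Multiple imputation does not help, because the problem lies in the recorded values.

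**2. How much does the baseline help?** Let the professionals' rating exceed the external unit's by a₀ at baseline and a₁ at 12 months, on the proportion scale, and let the true effect be d.

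- Difference in change from baseline: d + (a₁ − a₀). A constant offset (a₁ = a₀) cancels.
- Baseline-adjusted comparison with baseline slope β below 1: d + a₁ − βa₀. A constant offset a leaves (1 − β)a, so it cancels in part.
- A shift that appears only after counselling (a₀ = 0, a₁ = b): d + b. Nothing cancels.

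**3. What could an uncancelled shift b do?** Inputs from the Sample size section: 13 centres per arm, 140 participants per centre, 30% loss, ICC 0.01, alpha 5%. Assumptions of this review: no true effect, 50% in action or later in the control arm, an ICC for this outcome equal to the planning value, and a comparison of 12-month proportions.

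- Analysed per centre: 140 × 0.70 = 98. Per arm: 13 × 98 = 1274.
- Design effect: 1 + (98 − 1) × 0.01 = 1.97.
- Effective number per arm: 1274 / 1.97 ≈ 647.
- Standard error: SE = √{[p(1 − p) + (p + b)(1 − p − b)] / 647}.
- Probability of a significant result: P(|Z + b/SE| > 1.96).

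For b = 0.03: SE = √[(0.2500 + 0.2491) / 647] ≈ 0.0278, b/SE ≈ 1.08, probability ≈ 19%.

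For b = 0.05: SE = √[(0.2500 + 0.2475) / 647] ≈ 0.0277, b/SE ≈ 1.80, probability ≈ 44%.

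The control proportion is not given, so the range over other assumed values is:

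| Assumed proportion in action or later | b = 2 points | b = 3 points | b = 5 points |
|---|---|---|---|
| 20% | 14% | 26% | 58% |
| 30% | 12% | 21% | 49% |
| 40% | 11% | 20% | 44% |
| 50% | 11% | 19% | 44% |

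The nominal rate is 5%. These figures show how sensitive the comparison is to a shift. They do not predict the bias.

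**The case against.** The best case for the plan has five parts.

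- **Reach.** Stage of change is one of 18 listed secondary outcomes. The primary behaviours, the stated hypotheses and the sample size do not rest on it. This stands, and it sets the severity.
- **Baseline.** The assessor type is the same at both times within each arm, so a stable rating habit would largely cancel in a change score. This stands for a constant offset. It does not cover a rater who by month 12 has delivered the treatment.
- **Reason for the split.** Staging is part of the intervention, so the professionals must do it at the start. This stands as a reason for a clinical rating. It does not justify using that rating as the trial outcome, least of all at 12 months.
- **Cross-check.** The external unit measures the behaviours themselves in both arms, so disagreement between recorded stage and measured behaviour can be compared by arm. This is a useful diagnostic, but it does not turn two kinds of rating into one.
- **Blinding.** The external unit is not said to be blinded, so using it throughout would not remove all detection bias. This stands.

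A reader might go further and infer that the bias is known to favour the intervention, or that participants who changed are more likely to be rated at 12 months because they still see their professional. The documents support neither. They give no direction or size for an assessor effect. Table 4 schedules the rating at the 12-month follow-up, not under intervention visits, and gives no rate of contact with the professional by outcome.

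**Conclusion.** The point holds for one outcome. As planned, an arm difference in stage of change cannot be separated from an assessor difference, and the documents contain nothing that corrects this. The primary outcomes on diet, physical activity and smoking are not touched, so the main conclusion of the trial is not at risk from it.

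The size is unknown. If a shift of 3 to 5 points arose after counselling and did not cancel, about 19% to 44% of trials with no true effect would show a significant difference at an assumed 50% in action or later. Those figures rest on the planning ICC, on 30% loss and on an assumed shift. With a constant offset and baseline adjustment they would be lower. Severity is moderate: the flaw is worth correcting because the correction is cheap, but it does not threaten the trial's main inference.

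**What to change.** Change the stage-of-change row of Table 4 so that the external unit records stage for the outcome in both arms, with the same items, at its existing baseline and 12-month visits. Keep the professionals' rating in the intervention arm as a separate variable for tailoring, and exclude it from the arm comparison.

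The cost is one table row and a short set of items at visits that already take place, with no new staff and no new visit. Intervention participants would answer the stage items twice. The change removes the arm-specific assessor difference. It does not remove all detection bias, since no blinding is planned.

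The trial was registered retrospectively, so some baselines may already have been collected under the split arrangement. In that case, have the external unit record the 12-month stage in both arms and compare arms on that value. Do not form a change score from the professional-rated baseline, which would switch assessor within one arm only. Report the limitation with the result.

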### Analysis

#### Effectiveness of intervention

All analyses will be carried out in accordance with the intention-to-treat principle. Depending on the characteristics of the variables, it will be assessed if it is appropriate to make multiple imputationin the variables with missing data or to make a conservative approach to data loss. Multiple imputation will be the preferred technique for dealing with missing data, and the conservative approach will be used when the data indicate that it is the most appropriate. Multiple imputation by chaining equations procedure will be used to obtain at least 20 imputed datasets and Rubin’s rules will be used to combine them [72]. Sensitivity analyses will be performed for the primary and secondary outcomes to assess the impact of the multiple imputation or the conservative approach to data loss.

Descriptive and bivariate analyses will be calculated for all variables of interest. We will use cluster specific methods because PHC centres will be randomised. In order to analyse the effect of the intervention on each outcome measure, we will use hierarchical linear or logistic regressions models for clustered data. We will also analyse the variables associated with the change in the adherence to the Mediterranean diet, physical activity level and smoking cessation adjusting for possible confounding variables. Final models will be chosen coherently with the study objectives and the nature of the variables (potential confounders, significant and clinically relevant variables). The interactions and collinearity of the models will be evaluated. The size of the effect (Cohen’s d) will also be calculatedand the number needed to treat will also be calculated..

The level of significance of the models will be set at 5%. Stata/SE v.15 or higher (StataCorp, LP, TX) and R version 3.4.4 or higher will be used for statistical analysis.

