### Sample size

The sample size was calculated on the basis of data from the literature and some results of phase II. We expect a difference in the percentage of people who show a positive change in one or more of the three behaviours between the two groups of at least 8%. Assuming 30% patient loss to follow-up, alpha risk of 5%, beta risk of 20%, and an intracluster correlation of 0.01 [68], we consider that it is necessary to study a minimum of 140 participants for each PHC centre, a total of 3640 people (1820 for each of the two groups, 13 PHC centre per group). PASS software was used to compute the sample size [PASS 14 Power Analysis and Sample Size Software (2016). NCSS, LLC. Kaysville, Utah, USA, ncss.com/software/pass]. Sampling was done in order to fulfil an established sex and age quota which is proportional to the last general population census.

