### Assignment of intervention

The allocation schedule for random assignment of intervention to PHC centres will be computer generated at a central location (IDIAP Jordi Gol, Barcelona, Spain). For each of the seven Spanish Autonomous Communities, we will randomly allocate half of the PHC centres to the intervention group and the other half to the control group. In total, 13 PHC centres will be allocated to the intervention group and 13 other to the control group. The allocation will not be concealed at PHC centres and no blinding will be done.

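### The effectiveness analysis lets statistical significance guide the final models and does not tie the treatment effect to one prespecified model containing the randomisation stratum

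*Protocol article*

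**What the plan says.** In the protocol article, Analysis, Effectiveness of intervention, three statements follow one another.

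- On the treatment effect: "In order to analyse the effect of the intervention on each outcome measure, we will use hierarchical linear or logistic regressions models for clustered data". No covariate or stratum term is listed.
- On a second analysis: "We will also analyse the variables associated with the change in the adherence to the Mediterranean diet, physical activity level and smoking cessation", adjusted for possible confounders.
- On model choice: "Final models will be chosen coherently with the study objectives and the nature of the variables (potential confounders, significant and clinically relevant variables".

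The text then turns to interactions, collinearity, effect size, number needed to treat and the 5% level, without saying which of the two analyses each belongs to.

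Under Assignment of intervention: "For each of the seven Spanish Autonomous Communities, we will randomly allocate half of the PHC centres to the intervention group", with the other half going to control. Overall, "13 PHC centres will be allocated to the intervention group and 13 other to the control group".

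**The concern.** The model-choice sentence is a stated rule, so this is not a detail left to another document. It names significance as one criterion and stands under the heading that covers the treatment effect. If it applies there, the covariates beside the arm term depend on the data, and so does the reported effect. In a logistic model the conditional odds ratio also changes with the covariates kept, so even the quantity being estimated is not fixed in advance.

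The number of randomised units makes this matter. There are 26 centres, and Data collection and management lists about 17 centre-level characteristics (8 on the assigned population, 9 on organisation), all of them possible candidates.

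The same rule can remove the stratum. Allocation balanced within communities takes community differences out of the true sampling error of the arm contrast. A model without community leaves those differences in the estimated error, so the intervals are too wide.

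**Working it through.** **The plan's own figure.** Inputs from Sample size: an 8-point difference, 30% loss, alpha 5%, power 80%, ICC 0.01, 140 participants per centre, 13 centres per arm. The control rate is not given. I assume a two-sided test and 46% vs 54%, where the variance is near its maximum.

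- Completers per centre: 140 × 0.7 = 98. Design effect: 1 + (98 − 1) × 0.01 = 1.97.
- Per arm before clustering: (1.96 × √(2 × 0.5 × 0.5) + 0.8416 × √(0.46 × 0.54 + 0.54 × 0.46))² / 0.08² = 613 after rounding up. After the design effect: 1208. After loss: 1208 / 0.7 = 1725, against 1820 stated.
- With 13 centres per arm fixed: m = 613 × 0.99 / (13 − 6.13) = 88.3 completers, or 126 recruited per centre (136 with continuity correction), against 140 stated.
- Power at 140 per centre: 0.82 by normal approximation, 0.79 by t on 24 df.

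The stated size is reproduced closely, and this point does not alter it.

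**Selection by significance.** Simulated centre-level analysis with no treatment effect: 13 + 13 centres, 98 completers each, ICC 0.01, an assumed 45% rate, and candidate centre covariates that are pure noise. Covariates enter by forward selection at p < 0.05, and the arm is then tested by t.

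- No selection: type I error about 5%.
- 5 candidates: about 5% to 6%.
- 10 candidates: about 8%.
- 17 candidates: about 10%.

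One-step univariate screening stayed at about 5%. The size of the harm therefore depends on the selection procedure, which the article does not fix.

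**Dropping the stratum.** Let s be the share of between-centre variance explained by community. The documents do not give s, so I take a range. Further assumptions are communities of 4, 4, 4, 4, 4, 4 and 2 centres and 35% vs 43%. ICC is 0.01 with 98 completers per centre. There were 6000 runs of a centre-level linear analysis, with 24 df without community terms and 18 df with them. Type I error comes from the same set-up with no difference.

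| s | SE without → with | Power without → with | Type I error without → with |
|---|---|---|---|
| 0 | 0.0265 → 0.0264 | 0.82 → 0.81 | 0.050 → 0.051 |
| 0.25 | 0.0263 → 0.0247 | 0.83 → 0.85 | 0.036 → 0.049 |
| 0.50 | 0.0263 → 0.0230 | 0.86 → 0.90 | 0.029 → 0.046 |
| 0.75 | 0.0260 → 0.0210 | 0.87 → 0.94 | 0.017 → 0.050 |

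SE reduction from including community: 1 − 0.0247/0.0263 = 6% at s = 0.25, and 1 − 0.0210/0.0260 = 19% at s = 0.75. Expressed as an excess when it is omitted, these are 0.0263/0.0247 − 1 = 6% and 0.0260/0.0210 − 1 = 24%.

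**Cost of the stratum terms.** Seven communities use 7 − 1 = 6 between-centre df, so 24 becomes 18. At s = 0, t-based power goes from 0.791 to 0.779 (46% vs 54%) or from 0.810 to 0.799 (35% vs 43%), about one point.

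**The case against.** The strongest reply concerns scope. The model-choice sentence directly follows the one on variables associated with change and may describe only that analysis. If so, the separation asked for here is already intended. The text does not settle this, and significance is only one of three criteria. The ambiguity stands, but so does the need to resolve it, because one of the two readings puts selected covariates into the treatment effect.

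The second reply is that an article commonly leaves stratum terms to the full protocol or SAP. That is fair, and it rules out several stronger readings that a reader might infer.

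- *That the strata are left out of the analysis.* No sentence excludes them, and hierarchical models or potential confounders could include community. All that can be said is that no stratum term is named and the stated rule would permit its removal.
- *That a large-sample Wald z-test is planned and is too liberal.* No reference distribution is named.
- *That baseline values are omitted.* This is also silence.
- *That stratum adjustment lifts power from 82% to 87–91%.* Those figures are normal approximations with the ICC lowered to 0.0075 and 0.005 (0.869 and 0.914 against 0.823). They rest on a variance share and a control rate that the documents do not give, and they hold the comparator fixed although stratified allocation raises its power too. They also ignore degrees of freedom: moving from z to t on 18 df costs about 4 points (0.823 to 0.779). The simulated gain is 2 to 7 points for s of 25% to 75%, and none at 0%.

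Finally, the two effects pull in opposite directions. Stepwise selection can be liberal and omitting the stratum is conservative, so they must not be added together.

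**Conclusion.** The point holds as a flaw in how the model-choice rule is written. As it stands, the rule allows the treatment effect to depend on data-driven covariate selection with 26 randomised centres, and allows the randomisation stratum to be dropped. Selection can raise type I error to about 8% to 10% under forward selection among 10 to 17 noise covariates, and by nothing noticeable under simple screening. Dropping the stratum costs nothing if community explains none of the between-centre variance. At assumed shares of 25% to 75%, it takes type I error down to between 0.036 and 0.017 and forgoes a 6% to 19% smaller standard error. These sizes are illustrative: they rest on assumed control rates, community sizes and variance shares, and on a linear centre-level analysis standing in for the hierarchical logistic model. That community is omitted, or that a particular test is planned, is not established.

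**What to change.** State, before analysis, that the treatment effect for each effectiveness outcome comes from one prespecified hierarchical model: arm, Autonomous Community as a fixed effect, and a centre random intercept. Add the baseline value where it varies among those analysed, for example the PREDIMED score or the baseline of a continuous outcome. Smoking status among baseline smokers, or IPAQ level among those with low activity, is constant under the article's own outcome definitions and cannot serve as a covariate. Age and sex may be added by choice, but they are sampling quotas ("Sampling was done in order to fulfil an established sex and age quota"), not randomisation strata, so the design does not require them. Limit the sentence on significant variables explicitly to the analysis of variables associated with change.

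The cost is a change of wording, with no new data. Community terms use up to 6 between-centre degrees of freedom, about one power point if community explains nothing.
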